### Outcomes and data collection procedures

The *primary outcome* is change in Saint George’s Respiratory Questionnaire (SGRQ) Total Score at 4 and 12 months compared to baseline. The SGRQ is a well validated disease-specific HRQL measure [48] widely used in clinical trials of pulmonary rehabilitation, disease management interventions, and exercise [49] in patients with COPD. SGRQ will be measured at baseline, four months, and one year after randomization.

Hospitalizations for AECOPD, self-reported dyspnea, and change in average daily step counts will be *secondary outcomes*. To ascertain hospital admissions, a two-way process will be performed, using both self-reported hospitalizations (which capture non-VA admissions) and identifying hospital admissions through the VA administrative databases. ICD-9 codes will be used to identify cause of admission. AECOPD will be defined by a previously validated combination of inpatient and outpatient ICD-9 codes [50], and validated algorithms will also be used to identify pneumonias and episodes of respiratory failure [51,52]. Dyspnea is measured with the MMRC Dyspnea Score [53,54]. Change in average daily step counts will be calculated using 7 days where at least 5 of the 7 days have at least 100 steps and 8 hours of activity. Goal commitment (percentage of intervention days during which step-count goals are achieved, as well as self-reported goal commitment and perceived difficulty of goal level evaluated by the Likert scale and open-ended questions) and participant retention are also secondary outcomes. Endpoints are evaluated at baseline, four months, and one year after randomization.

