**Figure 3 F3:**
[figure not shown]
Example of the informational messages provided for participants in Taking Healthy Steps.

Participants are asked to wear the pedometer every day, from waking to sleeping, during the initial 16-week period of intervention, and are encouraged to continue wearing and uploading the data throughout the eight-month maintenance phase.

*Feedback* is provided in three ways: 1) participants can read their step-count data from the pedometer display throughout the day; after uploading step-count data to the website, they can select from a variety of detailed graphs displaying different views of their step counts, including weekly and daily views with daily or hourly step-count totals; 2) participants can look back at their graphs and goals from previous weeks; and 3) the website displays a textual message about their step-count average for the week.

*Goal-setting* is provided each week for the entire one-year intervention period, with participants receiving a new individually tailored and automatically calculated daily step-count goal. The algorithm for calculating step-count goals was developed based on a series of usability studies, pilot studies, and RCTs in participants with type 2 diabetes, coronary artery disease, and obesity [40,46]. This algorithm has been validated for use in similar populations [43]. The algorithm involves adding a fixed increment to the average step counts of uploaded pedometer data for the participant over the previous seven days. Because COPD patients tend to be less physically active and may find it more challenging to increase their step counts, the goal is never higher than a 600-step increment, rather than the 800- or 1200-step increments reported for other populations. Goals are rounded off to the nearest 100 steps, and the maximum possible goal is 10,000 steps per day. Each Sunday, the goal calculation algorithm is run and sends participants automated emails with their personalized daily step-count goal for the week, which appears in the step-count feedback section on the website, both in text form and graphs. Goals are not necessarily monotonically increasing. For example, if a participant is sick, and thus records low step counts for one week, the subsequent week’s goal might be lower than the goal for the week the participant was sick. A snapshot of the individual step-count webpage can be seen in Figure 4.

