### Wait list (control arm)

Wait list controls are notified that they are enrolled in the study, but that they will not be able to start the active intervention for one year. They are neither assigned step-count goals nor do they have access to the personalized dynamic website during the year long waiting period. However, they have access to a brief static webpage that provides a checklist of completed surveys and their week number in the study. Participants keep the study pedometer and are asked to log in monthly to report adverse events and to upload their pedometer data, with no other incentive to log into the website and no feedback of pedometer data or goal setting. They are given no specific instructions on exercise.

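### Step-count change could pick up a wear difference between arms: the 7-day mean does not clearly drop failing days, and after baseline daily wear is stated only for the intervention arm

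*Protocol article*

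**What the plan says.** The section on outcomes and data collection makes step-count change a secondary outcome, "calculated using 7 days where at least 5 of the 7 days have at least 100 steps and 8 hours of activity". The same section fixes the time points: "Endpoints are evaluated at baseline, four months, and one year after randomization".

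What participants are asked to do with the pedometer changes over time and by arm:

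- **Baseline, before randomization** (Baseline measures and randomization): everyone is asked for seven days of all-day wear, with the display covered and no feedback.
- **Intervention arm, first 16 weeks** (Pedometer-based, internet-mediated intervention): "Participants are asked to wear the pedometer every day, from waking to sleeping, during the initial 16-week period of intervention". This arm also has weekly goals, a readable display and step-count feedback.
- **Intervention arm, afterwards** (same section): participants "are encouraged to continue wearing and uploading the data throughout the eight-month maintenance phase".
- **Control arm, whole year** (Wait list): "Participants keep the study pedometer and are asked to log in monthly to report adverse events and to upload their pedometer data". By design nothing else draws controls to the site, and they get neither goals nor feedback on their steps. The section states no request to wear the device.

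**The concern.** Two features of the text combine.

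First, the outcome rule says when a 7-day window qualifies, but not what happens to the one or two days that may fail. Taken at its word, the calculation uses all seven. A day with the device in a drawer would then count as a day of almost no walking.

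Second, the outcome is a change from baseline, and the stated conditions of wear differ between arms only after baseline. Subtracting a baseline measured under equal conditions does not remove a difference in wear that arises at follow-up; it passes that difference into the result. If controls wear the device less, their step change falls with no change in walking.

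Walking is the behaviour that the programme is built to change. A step gain that was partly extra device wear would mislead readers about whether the programme changed behaviour, and about how any effect on quality of life came about.

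**Working it through.** **Plan's own figure.** The article gives no design figure for step counts. Its only sample-size calculation is for SGRQ, and it reproduces: with a difference of 4.3, SD 10, two-sided 0.05, 80% power and 2:1 allocation, the control arm needs 1.5 × (1.960 + 0.842)² × 10² / 4.3² ≈ 63.7, so 64, with 128 in the intervention arm, 192 in total. Allowing for 20% dropout, 192 / 0.80 = 240. Nothing below touches it.

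**Inputs from the article.** Baseline mean 3,497 steps/day, SD 2,220 (Results); at most 7 − 5 = 2 failing days in a qualifying week (outcome rule); 128 and 64 evaluable (sample size section).

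**Assumed.** The arm difference in wear, the steps recorded on failing days, the SD of step change, and (for step 5) waking hours.

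**Step 1: loss for one person if failing days stay in the mean.** With *k* failing days that record *s* steps each, and true walking unchanged, the loss is *k* × (3,497 − *s*) / 7.

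- *k* = 1, *s* = 0: 3,497 / 7 = 500 (14%), giving a mean of 2,997.
- *k* = 2, *s* = 0: 2 × 3,497 / 7 = 999 (29%), giving 2,498. This is the most that the rule allows.
- *k* = 1, *s* = 99 (just below the step threshold): 3,398 / 7 = 485.
- *k* = 1, *s* = 1,748 (a day that fails on hours but records half the usual steps): 1,749 / 7 = 250.

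The zero-step figures are therefore an upper bound.

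**Step 2: difference between arms.** If controls average *d* more zero-step failing days per week, the spurious difference is 3,497 × *d* / 7. The last column is the chance of a falsely significant result favouring the intervention, from a two-sided 0.05 normal test with standard error SD × √(1/128 + 1/64) = 0.153 × SD. It assumes an SD of step change from 1,500 to 2,220; the upper value borrows the baseline SD because the article gives none for change. Without bias this chance would be 2.5%.

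| *d* (assumed) | Spurious difference, steps/day | False-positive chance, SD 1,500 to 2,220 |
|---|---|---|
| 0.25 | 125 | 8% to 6% |
| 0.5 | 250 | 19% to 11% |
| 1 | 500 | 59% to 31% |

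For example, with *d* = 1 and SD 1,500 the standard error is 230, 500 / 230 = 2.18, and the chance is Φ(2.18 − 1.96) ≈ 0.59.

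**Step 3: timing.** Sixteen weeks of requested daily wear end close to the four-month assessment. At one year the intervention arm is only encouraged to wear the device, so the stated contrast is weaker, though the goals and feedback remain.

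**Step 4: the valid-days reading.** If failing days are dropped from both numerator and denominator, the artefact in steps 1 and 2 is zero.

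**Step 5: what remains under that reading.** Eight hours makes a day valid, while one arm is asked for waking-to-sleeping wear. Suppose 14 waking hours and an even step rate (both assumed). A valid day worn for *w* hours then loses 3,497 × (1 − *w*/14): about 500 steps at 12 hours, 999 at 10 and 1,499 at 8. These are losses per day for one person; the bias depends on how far worn hours differ between arms.

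**The case against.** **The rule may mean valid days only.** The sentence can be read as a test of whether a week qualifies, with the mean then taken over the qualifying days. A reader might infer that the trial definitely averages non-wear days; the text does not establish that. What stands is that the two readings give different numbers, and that the valid-days reading leaves the partial-wear problem in place.

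**Silence about controls is not proof of no prompt.** A journal article condenses its protocol, and a reminder before the assessment weeks could exist. It would go too far to say that failing days will differ by arm. Still, the article describes what each arm is asked to do with the pedometer, and the two descriptions differ on wear.

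**The size is not known.** A reader might take 500 steps/day as the expected artefact, or set it against the 600-step cap on the goal increment. Neither is supported. The 500 needs failing days kept in the mean, near-zero counts on them, and a full day's difference between arms. The cap limits a weekly goal; it is not an expected effect or an important difference.

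**Missing weeks need not favour the intervention.** One might infer that more excluded control weeks push the same way. Excluding weeks with fewer than five valid days could instead leave the more engaged and more active controls, which would work against the intervention. The direction is unknown.

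**It is a secondary outcome.** This is correct, and it limits the weight of the point.

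**Conclusion.** The point holds in a conditional form. The article's step-count rule does not clearly keep failing days out of the mean, and after an equal baseline it states daily wear for one arm only. Lower control wear at follow-up, chiefly at four months, could therefore show up as a step-count effect.

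If failing days are retained with about zero steps, the artefact is about 125 to 500 steps/day for an assumed arm difference of 0.25 to 1 non-wear day per week. It is smaller if failing days hold real steps, and zero from this source if only valid days are averaged. Under either reading a partial-wear bias can remain, and differential exclusion of weeks adds a bias of unknown direction.

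The article does not show that wear did differ, or that the quality-of-life result is at risk. The SGRQ outcome and the sample size stand. The change is worth making because the remedy is cheap.

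**What to change.** 1. State that the step-count mean is taken only over valid days, with at least five in the 7-day window, in the same way at baseline, month 4 and month 12.
2. Send both arms the same request for a 7-day wear week at months 4 and 12, matching the baseline request, and take the outcome from those weeks.
3. Report by arm, at each time point, the number of valid days, worn hours, and weeks excluded for too few valid days.
4. Add a sensitivity analysis adjusting for wear time, because items 1 and 2 do not remove partial-wear bias under the 8-hour rule.

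**Cost.** A wording change, two automated emails to people who already hold the device, and one extra analysis. The downside is slight extra prompting of controls, in a design that otherwise gives them no feedback or goals. All 239 participants are already randomized. For anyone whose month-4 week has passed (the article does not say how many), item 2 can apply only at month 12, and items 1, 3 and 4 must carry the month-4 result.

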### Conceptual framework

The Taking Healthy Steps intervention is based primarily on self-regulation theory. The Theory of Self-Regulation emphasizes an iterative, rational process of behavior change in which an individual working towards a behavioral goal learns from successes and failures and uses this knowledge to develop effective behavioral strategies to achieve his or her goal [37,38] (Figure 1). Accurate self-monitoring, goal setting, and feedback are critical components of the cycle of self-regulation. The Taking Healthy Steps intervention targets the cycle of self-regulation with four components: 1) step-count feedback from a pedometer and personal website, 2) automated, gradually incrementing goals, 3) tailored motivational messages, and 4) an online community to enhance social support. Participants upload detailed time-stamped step-count data. Tailored algorithms based on the data provide dynamic individualized incremental walking goals and feedback about success at meeting these goals. Goal setting is based on Lock and Latham’s demonstration that high, hard goals improve performance as long as the goals are not too high [39]. Goal increment is based on a series of pilot studies in individuals with a variety of chronic illness [40]. Online communities allow users to interact with each other by posting messages for others to read and by reading messages posted by others. These communities are useful for individuals who report low baseline social support, which is a predictor of poor adherence to physical activity interventions.

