## Discussion

Patients with COPD experience progressive deterioration in their functional status, HRQL, and ability to exercise. Although continuous exposure to tobacco and poor lung function are strong factors related to poor outcomes in this population, the presence of comorbidities has emerged as a significant factor associated with all unfavorable COPD outcomes. Lack of physical activity is both a consequence and a mediator of COPD outcomes, and the success of pulmonary rehabilitation in decreasing hospital admissions, improving HRQL, and decreasing dyspnea has made rehabilitation one of the cornerstones of COPD management. Unfortunately, many barriers limit initial participation in rehabilitation, and there is a need for reinforcement to maintain the gains achieved by patients after completion of a formal program. Veterans with COPD face these barriers, which are complicated by the high frequency of rural residency, comorbidity, and unemployment in this population. Building on previous research that has shown the feasibility of using a pedometer by COPD patients, the accuracy of the device, the ability to individualize and have feedback of an automated intervention, and patients’ favorable views towards participating in online communities, we designed the current pedometer-enhanced, Internet-mediated clinical trial of physical activity for Veterans with COPD. The clinical trial includes unique characteristics such as identification of the pool of potential participants using administrative databases, remote orientation on the use of the pedometer, patient-initiated acquisition of medical clearance for participation, automated web-based data collection, use of multiple communication tools (e.g. pedometer, participation in online communities), and a dynamic, adaptive algorithm for step-count goals.

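### The step-count validity rule is framed as hours of activity, so on its natural reading very inactive weeks can go missing because they are inactive; a sensitivity analysis should sit beside it

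*Protocol article*

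**What the plan says.** All references are to the protocol article.

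- **Outcomes and data collection procedures** lists the step endpoint among the secondary outcomes: "Hospitalizations for AECOPD, self-reported dyspnea, and change in average daily step counts will be *secondary outcomes". The change is computed "using 7 days where at least 5 of the 7 days have at least 100 steps and 8 hours of activity". On timing, "Endpoints are evaluated at baseline, four months, and one year after randomization".
- **Conceptual framework** describes the device data: "Participants upload detailed time-stamped step-count data".
- **The section on the intervention** (text after Figure 3) mentions website graphs, "including weekly and daily views with daily or hourly step-count totals". It also gives the wear request: "Participants are asked to wear the pedometer every day, from waking to sleeping, during the initial 16-week period of intervention". Its account of goal-setting gives the example of a participant who falls ill and so has a week of low counts.
- **Discussion** describes the disease course: "Patients with COPD experience progressive deterioration in their functional status, HRQL, and ability to exercise".

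The validity rule is phrased in terms of activity. The article gives no separate wear-time criterion.

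**The concern.** A validity rule for a pedometer week is meant to screen out non-wear. This one uses the quantity being measured. With time-stamped steps, the most natural meaning of the eight-hour condition is eight hours of the day in which steps were recorded. A patient who wears the device from morning to night but sits through most hours then fails the day. Three such days make the week unusable. Whether the outcome exists therefore depends partly on its value, even with perfect and equal wear in both arms. The 100-step floor is lenient; the hours condition is the one that bites.

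The article itself supplies a mechanism: illness lowers counts, and function deteriorates over time. If the weeks lost are mainly those of patients who declined, the observed mean change is too favourable. If the programme works, such weeks should be commoner in controls, so the control decline would be partly hidden and the between-arm difference pulled towards zero. Step change is the direct check on whether a walking programme changed walking.

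**Working it through.** **1. The plan's own figure.** The article gives no power or missing-data figure for steps. Its sample size rests on SGRQ change (difference 4.3, SD 10, two-sided 0.05, 80% power, 2:1):

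n(control) = (1 + 1/2) × (1.960 + 0.842)² × 10² / 4.3² = 1.5 × 7.849 × 100 / 18.49 = 63.7, so 64. The total is 3 × 64 = 192, and 192 / 0.8 = 240.

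This reproduces the article's figures. Nothing in it depends on the step rule.

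**2. The weekly gate.** Let q be the chance that a day fails, with days independent (assumption).

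P(week usable) = Σ C(7,k) (1−q)^k q^(7−k), k = 5 to 7

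| q | 0.1 | 0.2 | 0.3 | 0.4 | 0.5 |
|---|---|---|---|---|---|
| Week usable | 97% | 85% | 65% | 42% | 23% |

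**3. From active hours to usable weeks.** Assumptions, none given in the article: full wear, H waking hours, each with independent probability p of any recorded step, and the 100-step floor always met. Then P(day qualifies) = P(Binomial(H, p) ≥ 8), which goes into the formula in step 2 as 1 − q.

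| p | H = 12 | H = 14 | H = 16 |
|---|---|---|---|
| 0.7 | 70% | 98% | 99.9% |
| 0.6 | 14% | 63% | 93.5% |
| 0.5 | 0.4% | 9% | 42% |
| 0.4 | about 0% | 0.1% | 2.3% |

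For p = 0.5 the daily probabilities are 0.194, 0.395 and 0.598. Usability falls steeply with activity in every column, but where it falls depends heavily on the assumed H.

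**4. What this could do to mean change.** This is an illustrative simulation. Baseline steps are lognormal with the article's mean 3,497 and SD 2,220. Assumed: day-to-day variation with a log-scale SD of 0.4; 16 waking hours; P(hour active) = 1 − exp(−daily steps / (16 × k)), where a larger k means steps bunched into fewer hours; 15% of patients decline and the rest are stable. Mean change is taken among patients with a usable baseline week.

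| Decliners fall to | k | Follow-up week usable: decliners / stable | True mean change | Observed mean change | Decline hidden |
|---|---|---|---|---|---|
| 30% of baseline | 50 | 69% / 99.5% | −371 | −328 | 43 |
| 30% | 100 | 30% / 96% | −403 | −219 | 184 |
| 30% | 150 | 14% / 90% | −465 | −143 | 322 |
| 50% | 50 | 91% / 99.5% | −264 | −258 | 6 |

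The direction is the same in every row. The size runs from 6 to 322 steps/day on inputs that the article does not supply.

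**The case against.** Several stronger readings are tempting, and the article does not support them.

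- **That failing days are removed from the average.** The rule qualifies a 7-day window and tolerates up to two failing days. It does not say those days leave the mean. Under the model in step 3 with 14 waking hours, active hours on qualifying days exceed the patient's own mean by 11%, 26% and 52% at p = 0.6, 0.5 and 0.4. That inflation enters the endpoint only if failing days are also dropped. Nor does the text say how the window at each visit is chosen, so one bad week need not cost a patient the outcome.
- **That the phrase can mean only hours with steps.** It could also mean the span from first to last recorded step, which the same time stamps give. On that reading most of the concern goes. A condensed article may leave the operational definition to a fuller document.
- **That many patients sit near the limit.** Daily totals do not determine active hours. The mean is 3,497 / 14 ≈ 250 steps per hour over an assumed 14 hours. One SD below it, 3,497 − 2,220 = 1,277 still gives about 91 per hour, and an active hour may need only one step. Steps may cluster, but no hourly distribution is given.
- **That the arms must differ.** Attenuation needs an effective programme, control declines deep enough to fail whole weeks, and continued wear.

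It is also true that a pedometer cannot separate stillness from non-wear. A span rule would accept a device worn briefly morning and evening, possibly more often in controls, who get no feedback. Replacing the rule outright would trade one error for another.

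What stands is that the article states the rule, so this is not a missing detail, and that on its natural reading the exclusion is tied to the outcome.

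**Conclusion.** The concern holds in a limited form. If the eight-hour condition means hours with recorded steps, markedly inactive weeks become missing for an outcome-related reason. Decline in steps is then understated, and the between-arm difference is attenuated if decline is commoner in controls. The loss is of weeks, and of patients without a usable week; the article does not establish a loss of individual days.

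The size cannot be calculated from the article. It depends on waking hours, on how steps spread over the day and on how deep the decline is. It may be negligible, or it may hide most of the decline in the least favourable scenario tried (322 of 465 steps/day). Only a secondary outcome is affected; the SGRQ primary outcome and the sample size are not.

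**What to change.** Keep the stated rule. In the section on outcomes and data collection procedures, add:

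1. A sensitivity analysis of the between-arm step change under validity rules that do not depend on the number of active hours, still requiring 5 of 7 days. One version uses the 100-step floor alone. A second also requires at least 8 hours between the first and last recorded step of the day.
2. A table, by arm and visit, of how many patients and weeks the eight-hour rule excludes.

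If the results agree, the concern is closed; if they differ, the reader can see that the step result depends on the rule. Both items use data already uploaded. The cost is slightly more analysis. The relaxed rules will count some partly worn days as valid, which is why they should stand beside the stated rule and not replace it.
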